#### Both treatments

After treatment, both the deep venous system and the treated SSV are scanned by ultrasound.

A compression stocking (20 to 30 mmHg) will be applied for 24 hours continuously and for 2 weeks during the daytime. Patients are asked to resume normal activities immediately after the procedure. No concomitant phlebectomy or sclerotherapy are performed during the first 4 weeks of follow-up. Concomitant treatment after 4 weeks is reported in trial results.

### Follow-up

After 4 weeks, 1 year, 2 years and 5 years, patients are seen at the outpatient clinic to determine the anatomical and clinical success (Table 1). Ultrasound duplex imaging, VCSS, CEAP score and health status is measured at all aforementioned time points. Ultrasound duplex imaging is done according to a standardized protocol for all participating hospitals.

**Table 1 Tab1:** **Follow-up chart**

	Study period					
	Screening	Procedure	4 wk	1 yr	2 yr	5 yr
**Outpatient visit**	X		X	X	X	X
**Physical examination**	X		X	X	X	X
**Informed consent**	X					
**Inclusion criteria**	X					
**Randomization**	X					
**CEAP/VCSS**	X		X	X	X	X
**Ultrasound**	X		X	X	X	X
**Pain score**		X	X			
**AVVQ**	X		X	X	X	X
**SF-36**	X		X	X	X	X

AVVQ, Aberdeen Varicose Vein Questionnaire; CEAP, Clinical Etiology Anatomy Pathophysiology classification; SF-36, Short Form 36-Item Health Survey; VCSS, Venous Clinical Severity Score.

Post-procedural pain is evaluated using a linear VAS score of 0 to 100 mm during the 2 weeks after treatment. After 4 weeks follow-up, any small branch varicosities may be treated when indicated.

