**Discussion:**

The hypothesis of the MESSI trial is that the anatomic success rate of MOCA™ is not inferior to RFA. The second hypothesis is that post-procedural pain is significantly less after MOCA compared to RFA.

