### Sample size calculation

Power analysis is calculated for anatomical success at 1 year follow-up after endovenous treatment of the SSV. The calculation is based on the hypothesis that MOCA™ will have no inferior occlusion rates at 1 year after treatment compared to RFA. The meta-analysis by Van de Bos *et al*. showed anatomical success rates of 88% after RFA [10]. Our recent study on MOCA™ in SSV showed an occlusion rate of 97% in the group treated according to our current study protocol [17]. A Chi-square test with a one-sided 0.05 significance has a power of 80% to observe no difference between both groups, when each group consists of 74 patients (non-inferiority principle, range 2%). The study population of both groups will consist of 148 patients. Corrected for 7.5% lost to follow-up, the total study population will consist of 160 patients.

Pain is an important secondary outcome parameter. A sample size calculation is also performed for this endpoint based on the hypothesis that MOCA™ will have lower post-procedural pain scores, as measured by a 100-point pain score, during the first two weeks after surgery. To evaluate a 30 percent reduction in post-procedural pain, 58 patients per group are needed (alpha 5%, power 80%). This analysis will be performed after inclusion and randomization of at least 58 patients in each group.

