### Secondary endpoints

Post-procedural pain is evaluated using a 100-millimeter visual analog scale (VAS) during the first 2 weeks after treatment. The other secondary endpoints are initial technical success, clinical success, pain during treatment, complications and duration of the procedure. Initial technical success is defined as the ability to position the device adequately, treat the veins as planned and occlude the treated vein directly after the procedure proven by duplex ultrasonography. Clinical success is measured using the Venous Clinical Severity Score (VCSS). Complications related to the endovenous treatment, that occur within 30 days after treatment, are divided between major complications (deep venous thrombosis, pulmonary embolism, nerve injury, skin burn), minor complications (ecchymosis, superficial thrombophlebitis, hyperpigmentation, wound infection, prolonged pain >1 week) and sclerosans-related complications. Additionally, all endpoints will be evaluated at 2 and 5 years post-treatment.

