### Recruitment

A total of 160 patients with primary SSV insufficiency will be included in the MESSI trial after signing informed consent (Figure 1). Before treatment begins, a vascular surgeon or dedicated physician assistant will perform a physical examination. The Clinical Etiology Anatomy Pathophysiology (CEAP) score [18] and VCSS [19] are determined. Insufficiency of the SSV is defined by duplex ultrasound as a retrograde flow >0.5 seconds after calf compression while standing [20].

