### Statistical analyses

The study results will be evaluated based on intention-to-treat analysis. Data concerning the 1, 2, and 5 years follow-up will be analyzed for both study groups on an intention-to-treat manner by student t-test (normal distribution) or Mann Whitney U-test (skewed distribution). To test for normality, the Kolmogorov-Smirnov test will be used. The Chi-square test will be used for binomial data. All probability values are two-tailed. *P* <0.05 will be considered significant. Obliteration rates will be presented as Kaplan Meier curves, including censoring in case of loss to follow-up.

An interim analysis will be performed after treatment and at 4 weeks follow-up for the first 80 patients to monitor the progression of the study. Final analysis will be performed after follow-up of the last patient included in this study is completed.

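### Post-procedural pain, the separately powered second hypothesis, has no pre-treatment VAS and no stated baseline adjustment; the cost is some precision, not validity

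*Protocol article*

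**What the plan says.** **Status of pain.** The abstract says: "The second hypothesis is that post-procedural pain is significantly less after MOCA compared to RFA". Study objectives makes pain the secondary aim. Sample size calculation gives it a separate calculation: a 30 percent reduction, 58 patients per group, with "alpha 5%, power 80" percent.

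**When pain is scored.** Secondary endpoints: "Post-procedural pain is evaluated using a 100-millimeter visual analog scale (VAS) during the first 2 weeks after treatment". The text under Table 1 repeats this: "Post-procedural pain is evaluated using a linear VAS score of 0 to 100 mm during the 2 weeks after treatment". In Table 1 the pain row is marked under Procedure and 4 wk, and Screening is blank. Secondary endpoints also lists pain felt during the procedure as an outcome of its own: "The other secondary endpoints are initial technical success, clinical success, pain during treatment, complications and duration of the procedure". That is the natural explanation of the Procedure mark.

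**What is measured before treatment.** Recruitment: "The Clinical Etiology Anatomy Pathophysiology (CEAP) score [18] and VCSS [19] are determined". Table 1 and Health status measurement add AVVQ and SF-36, and Table 1 adds ultrasound.

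**Analysis.** Statistical analyses names the t-test or Mann-Whitney test for continuous data, in a sentence about the 1, 2 and 5 year results, and adds: "All probability values are two-tailed". No baseline covariate is mentioned for pain.

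**The concern.** Among the scales scored repeatedly, pain alone lacks a starting value, yet it carries a hypothesis with its own sample size. A VAS taken in the two weeks after treatment records whatever pain the patient has. That can include leg pain present beforehand, particularly as no phlebectomy or sclerotherapy is done in the first 4 weeks. If existing pain varies between patients and tracks the later score, it adds variance that a baseline reading would remove.

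Three things are at stake: the precision of the pain comparison, the ability to correct a chance imbalance directly, and a reference level when a lasting pain score is being interpreted. The data-collection schedule decides this. An analysis plan could still name VCSS or AVVQ as a covariate, but it cannot recover a VAS that was never taken.

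**Working it through.** **1. Inputs.** From Sample size calculation: 58 per group, alpha 5%, power 80%, 30% relative reduction. From Statistical analyses: two-sided testing. From Recruitment and Randomization: 160 patients allocated 1:1, so 80 per arm. The article gives no mean or SD for pain and no correlation ρ between baseline and later pain, so ρ is an assumption shown as a range.

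**2. The plan's own figure.** Without a mean or SD, the 58 cannot be reproduced forward, only solved backwards. With a normal approximation:

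d = (z₀.₉₇₅ + z₀.₈₀) × √(2/n) = (1.960 + 0.842) × √(2/58) = 0.520 SD

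A 30% reduction equals 0.520 SD if SD/mean in the RFA arm is 0.30/0.520 = 0.577. This step only calibrates the next one; the 58 is not disputed.

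**3. Gain from a baseline covariate.** Analysis of covariance multiplies the residual variance by (1 − ρ²), so:

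power = Φ( d × √(n/2) / √(1 − ρ²) − 1.960 )

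Example at n = 58, ρ = 0.3: 0.520 × √29 = 2.802; 2.802/√0.91 = 2.937; Φ(0.977) = 0.836.

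| Assumed ρ | Variance removed | Power, 58 per arm | 58 × (1 − ρ²), rounded up | Power, 80 per arm |
|---|---|---|---|---|
| 0 (no adjustment) | 0% | 80.0% | 58 | 91% |
| 0.1 | 1% | 80.4% | 58 | 91% |
| 0.2 | 4% | 81.6% | 56 | 92% |
| 0.3 | 9% | 83.6% | 53 | 93% |
| 0.5 | 25% | 89.9% | 44 | 97% |

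The fourth column is the number per arm that, with adjustment, does the work of 58 without it.

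**4. Validity without a baseline.** In 20,000 simulated trials with no treatment effect, 58 per arm and ρ = 0.5, an unadjusted t-test had a type I error of 4.9% and a mean difference of 0.000 SD. The omission causes neither bias nor a false-positive excess.

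**The case against.** The strongest reply is that nothing here is an error. The endpoint is pain after the procedure, not change from baseline. Allocation is randomised 1:1 within centre, so existing pain is balanced in expectation. The size of the gain rests on an undocumented correlation between existing leg pain and pain after a procedure, which may be low: at 0.2 or less, the gain is under 2 points of power. The trial enrols 80 per arm, where unadjusted power is already about 91%. All of this stands, and it keeps the point minor.

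It could also be said that the article is condensed and that the case report form may hold a score taken just before puncture under the Procedure mark. That is possible, but nothing in the text shows one.

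Four stronger readings are tempting, and the documents do not support them:

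- *Existing pain cannot be adjusted for.* VCSS, AVVQ and SF-36 are collected before treatment and can serve as covariates. They are a different scale, so adjustment is indirect, but it is available.
- *All patients enter with painful legs.* Inclusion criteria require C2 to C5 varicose veins but no symptoms, and Background says complaints start at the cosmetic.
- *Prolonged pain beyond a week cannot be told from existing pain.* Secondary endpoints counts only treatment-related complications. The adverse-event section excludes disease present at enrolment but requires worsening to be reported. Attribution is partly handled; a starting VAS would only make it firmer.
- *The 30% effect is diluted and power collapses.* If unaffected existing pain were 10%, 20% or 30% of the RFA mean, a 30% reduction in procedure-related pain would show as 27%, 24% or 21%, with power of 71%, 61% or 50% at 58 per arm. These shares are pure assumption, and covariate adjustment would not restore the diluted difference.

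**Conclusion.** The point holds as a minor design improvement. The schedule gives the second hypothesis no pre-treatment value on its own scale, and the article states no adjustment for another baseline symptom measure. The between-arm comparison is valid as planned. The loss is precision: at 58 per arm, from almost nothing (ρ = 0.1) to about 10 points of power (ρ = 0.5); at 80 per arm, about 2 to 6 points for ρ between 0.3 and 0.5. These figures assume a two-sided 5% test, an approximately normal pain summary, and that 58 per arm does give 80% power. They should not be read as showing that the pain result would be biased or uninterpretable.

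**What to change.** Add a Screening mark to the pain row of Table 1: one 0 to 100 mm VAS for the index leg, completed before the web-based randomisation. Analyse the two-week VAS by analysis of covariance with that score and centre as covariates.

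For patients enrolled before the change, either fill the missing baseline with the overall mean and add a missing-value indicator, which is acceptable because the covariate precedes randomisation, or adjust for the baseline AVVQ or VCSS already collected. Fix this choice before the pain data are compared by arm.

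The cost is a short amendment and one extra line at a visit where patients already complete AVVQ and SF-36. Enrolment began in the second quarter of 2014 and was expected to end in the third quarter of 2015, so only later patients would have the VAS and the gain would be partial.

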### Health status measurement

Health status will be measured according to the following:Short Form-36 (SF-36) is a multidimensional measurement of general health. It yields eight domains of functional health and well-being scores.Aberdeen Varicose Vein Questionnaire [22] (AVVQ) is a validated disease-specific health status measurement for chronic venous insufficiency (patient reported outcome).

Both the SF-36 and AVVQ questionnaires are completed pre-procedural and after 4 weeks, 1 year, 2 years and 5 years of follow-up.

### Data collection and management

All data will be collected at each participating treating center by case report forms (CRFs). Photocopies of the CRFs will be sent to the coordinating investigator (DB). The data will be entered in a validated data management system (Research Manager, NOVA Business Software, Zwolle, The Netherlands) and controlled by an independent monitor. The participating centers will be informed about the current status of recruitment and adverse events via a newsletter every month. Additionally, there will be regular contact between the principle investigator and the local investigators from the participating centers.

### Statistical analyses

The study results will be evaluated based on intention-to-treat analysis. Data concerning the 1, 2, and 5 years follow-up will be analyzed for both study groups on an intention-to-treat manner by student t-test (normal distribution) or Mann Whitney U-test (skewed distribution). To test for normality, the Kolmogorov-Smirnov test will be used. The Chi-square test will be used for binomial data. All probability values are two-tailed. *P* <0.05 will be considered significant. Obliteration rates will be presented as Kaplan Meier curves, including censoring in case of loss to follow-up.

An interim analysis will be performed after treatment and at 4 weeks follow-up for the first 80 patients to monitor the progression of the study. Final analysis will be performed after follow-up of the last patient included in this study is completed.

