### Randomization

Patients will be randomized directly after inclusion by the treating vascular surgeon or physician assistant to one of the treatment arms, using a validated web-based randomization tool (Research Manager, NOVA Business Software, Zwolle, The Netherlands). The 1:1 randomization is performed by blocks of ten with stratification for participating centers.

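### Intention-to-treat is the only analysis set named for the non-inferiority claim, and the 1-year result needs a per-protocol companion, a check on missing scans and visit-based reporting of occlusion

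*Protocol article*

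**What the plan says.** The Study objectives and Sample size calculation sections set a non-inferiority aim for occlusion at 1 year, with a margin of 2 percentage points and planning rates of 88% (RFA) and 97% (MOCA).

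On the analysis set, Statistical analyses states: "The study results will be evaluated based on intention-to-treat analysis". The abstract says the same. No per-protocol or as-treated analysis is named beside it.

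On losses, Sample size calculation needs 74 per group, 148 in all, and then adds: "Corrected for 7.5% lost to follow-up, the total study population will consist of 160 patients". Statistical analyses assigns binary outcomes to a chi-square test and adds: "Obliteration rates will be presented as Kaplan Meier curves, including censoring in case of loss to follow-up".

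On timing, Randomization says: "Patients will be randomized directly after inclusion by the treating vascular surgeon or physician assistant to one of the treatment arms". Table 1 places randomization in the screening column, ahead of the procedure. The same table and the Follow-up section schedule duplex scans at 4 weeks and at 1, 2 and 5 years; Both treatments adds a scan directly after the procedure.

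**The concern.** In a superiority trial, intention-to-treat is the cautious choice because departures from allocation pull the arms together. In a non-inferiority trial the same pull works towards the claim. Patients here are randomized before the procedure, so some may go untreated or receive the other device, and the plan names no second set that would reveal such an effect.

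The margin is also very small in patient terms compared with the losses the plan expects. The conclusion could depend on the status of a few veins that were not scanned at 1 year.

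Finally, a recanalisation is seen only when the patient is next scanned. If the Kaplan-Meier curve uses visit dates, failures are placed later than they occurred, and the curve read at exactly 1 year looks better than the truth. The risk is an over-favourable statement about MOCA or about occlusion in general.

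**Working it through.** **Inputs from the protocol.** RFA 0.88, MOCA 0.97, margin 0.02, one-sided 0.05, power 80%, 74 per group, 160 randomized 1:1, 7.5% loss.

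**Reproducing the plan's figures.** The Farrington-Manning formula is n = [(z₀.₉₅·s₀ + z₀.₈₀·s₁)/(0.97 − 0.88 + 0.02)]². Here s₁ = √(0.88·0.12 + 0.97·0.03) = √0.1347 = 0.3670. The rates restricted to a 2-point deficit are 0.9288 and 0.9088, so s₀ = √(0.9288·0.0712 + 0.9088·0.0912) = 0.3860. Then n = [(1.645·0.3860 + 0.842·0.3670)/0.11]² = 73.6, so 74 per group, as stated. With losses, 148/(1 − 0.075) = 160, also as stated.

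**Margin against losses.** 0.02·74 = 1.48 patients, or 0.02·80 = 1.6. Losses: 160 − 148 = 12, taken as 6 per arm (even split assumed).

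**Dilution under intention-to-treat.** Take a true deficit of exactly 2 points (0.86 v 0.88) and a crossover fraction x each way. The protocol gives no crossover rate, so x is assumed. The intention-to-treat difference is −2·(1 − 2x) points: −1.8 at x = 5% and −1.6 at x = 10%. With 74 per arm the standard error is about 0.0553, so type I error is Φ(−1.645 + 0.002/0.0553) = 5.4% and Φ(−1.645 + 0.004/0.0553) = 5.8%.

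**Missing 1-year scans at the planning rates.** Observed results are taken as 72/74 (MOCA) and 65/74 (RFA), with 6 lost per arm. The lower bound is d − 1.645·√(p₁(1 − p₁)/n + p₂(1 − p₂)/n), with d = MOCA minus RFA. Non-inferiority needs a bound above −2 points.

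| Treatment of the lost patients | MOCA | RFA | d (points) | Lower bound (points) |
|---|---|---|---|---|
| Left out | 72/74 | 65/74 | +9.5 | +2.5 |
| All failures | 72/80 | 65/80 | +8.8 | −0.3 |
| All successes | 78/80 | 71/80 | +8.8 | +2.3 |
| 3 of 6 MOCA open, 5 of 6 RFA occluded | 75/80 | 70/80 | +6.3 | −1.3 |
| 4 of 6 MOCA open, 5 of 6 RFA occluded | 74/80 | 70/80 | +5.0 | −2.8 |
| All MOCA failures, all RFA successes | 72/80 | 71/80 | +1.3 | −6.8 |

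Worked example, fifth row: √(0.925·0.075/80 + 0.875·0.125/80) = 0.0473, and 0.050 − 1.645·0.0473 = −0.028. Five of six occluded is close to the 88% planning rate for RFA (0.88·6 = 5.3).

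**Visit-dated Kaplan-Meier curve.** Assume 12% failure, every failure first seen at the 1-year scan, and scan dates spread evenly over day 365 ± 28. None of this is in the protocol. By day 365 half the scans are done.
- If patients with occluded veins stay at risk until later visits: S(365) = 1 − 0.12/2 = 0.94.
- If they are censored at their 1-year scan, the hazard acts on a shrinking risk set: S(365) = 0.5^0.12 = 0.92.
- If patients stay at risk and the curve is read at day 393, when the window closes: 0.88, the true rate.

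**The case against.** The best defence has four parts.

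- **Dilution is minor.** On the assumed crossover rates it adds less than one point of type I error, and the protocol gives no reason to expect more. This stands. Requiring both sets to agree is a safeguard, not the correction of a large bias.
- **The plan is not shown to drop lost patients.** A reader might infer from the sizing on 148 that the chi-square test uses complete cases only, so that the analysis is not truly intention-to-treat. The document does not say so. Adding patients for expected loss is routine, and the test can be run on 80 per arm once missing scans are classified. A general missing-data rule, such as imputation, may sit in an analysis plan that is not shown, so its absence is not an error here.
- **The Kaplan-Meier curve is a presentation.** A reader might see two rival estimates of the primary endpoint. Nothing says the non-inferiority verdict is read from the curve, and censoring losses in such a display is ordinary. The 92 to 94% also rests on an assumed window and on reading at exactly day 365. What stands is that scans at fixed visits suit a visit-based report better.
- **Comparing the margin with the losses exaggerates the fragility.** At the planning rates the distance to the margin is 11 points, or 0.11·74 = about 8 patients. Any rule applied alike to both arms keeps the bound above −2 at one-sided 0.05 in the table. Losing the claim takes 4 open veins among 6 lost MOCA patients, against a planned failure rate of 3%. This stands for the planning rates.

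One figure does not belong to this point. With all losses as failures, a two-sided 95% bound is 8.75 − 1.96·5.504 = −2.04 points, just past the margin. That arises because the sample size is one-sided while Statistical analyses states: "All probability values are two-tailed". It is a separate inconsistency.

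**Conclusion.** The point holds in limited form. The protocol affirmatively fixes intention-to-treat as the only set for a non-inferiority claim, and that set is not the conservative one. Its own effect is small: type I error of about 5.4 to 5.8% under 5 to 10% crossover each way.

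The result at the planning rates is robust when losses are treated alike (bounds −0.3 to +2.3 points). It is not robust to different failure rates among the lost: 3 of 6 open MOCA veins still pass (−1.3) and 4 of 6 do not (−2.8), given 5 of 6 RFA veins occluded. That rests on 72/74 v 65/74 observed and 6 losses per arm. It shows that robustness to missing scans should be demonstrated, not that the conclusion will be wrong.

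The Kaplan-Meier remark concerns reporting: an overstatement of 4 to 6 points at day 365 under the assumed window, with no effect on the chi-square test. The change is worth making before 1-year data are analysed, because it is cheap and guards against a falsely favourable verdict.

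**What to change.** 1. Keep intention-to-treat, with patients analysed in the arm to which they were randomized.
2. Add a per-protocol analysis (treated as allocated, 1-year duplex available) and state that non-inferiority is claimed only if the two analyses lead to consistent conclusions.
3. Add a tipping-point table for missing 1-year scans: the lower bound for each number of open veins among the lost MOCA patients against each number among the lost RFA patients, with the cells that cross −2 points marked.
4. Report obliteration by scheduled visit (4 weeks and 1, 2 and 5 years), or with an interval-censored estimator, in place of a Kaplan-Meier curve dated by visit.

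The cost is a few sentences in Statistical analyses, some extra tables, and a small loss of power from requiring both sets to agree. No additional patients or visits are needed.

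### Separate two-group tests at 1, 2 and 5 years leave out patients without a score at that visit, so the late VCSS, AVVQ and SF-36 comparisons may be biased if loss differs by arm

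*Protocol article*

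**What the plan says.** The Statistical analyses section states: "Data concerning the 1, 2, and 5 years follow-up will be analyzed for both study groups on an intention-to-treat manner by student t-test". The sentence goes on to give the Mann-Whitney U test for skewed data; binomial data go to a chi-square test. It adds that "All probability values are two-tailed", at the 5% level. The section names no score. The link to VCSS, AVVQ and SF-36 comes from elsewhere:

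- Follow-up, on the visits at 4 weeks, 1, 2 and 5 years: "Ultrasound duplex imaging, VCSS, CEAP score and health status is measured at all aforementioned time points".
- Health status measurement: "Both the SF-36 and AVVQ questionnaires are completed pre-procedural and after 4 weeks, 1 year, 2 years and 5 years of follow-up".
- Recruitment, on the examination before treatment: the CEAP score "and VCSS [19] are determined".
- Secondary endpoints: clinical success is measured by VCSS, and all endpoints are to be evaluated again at 2 and 5 years.

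Loss to follow-up appears twice. The sample size for the 1-year primary endpoint is "Corrected for 7.5% lost to follow-up", and for occlusion the plan says: "Obliteration rates will be presented as Kaplan Meier curves, including censoring in case of loss to follow-up". No loss figure is given for 2 or 5 years.

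**The concern.** A t-test or Mann-Whitney U test at a single visit needs a value from each patient it compares. Unless values are imputed, a patient who misses the 5-year visit is not in the 5-year comparison, whatever the analysis is called. The intention-to-treat label then describes which arm a patient is counted in, but does not secure a comparison of everyone randomised.

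By 5 years each patient should already have scores from screening, 4 weeks, 1 year and 2 years. The named tests use none of them, although they carry information about what the missing score would have been. If patients who do badly (or well) stop attending more in one arm than the other, the late difference shifts in a direction the test cannot reveal. The Discussion hypothesises comparable clinical success, and long-term results are to be published, so the shift could wrongly support or wrongly contradict a claim the trial intends to make.

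**Working it through.** **The plan's own figures.** 148 / (1 - 0.075) = 160, so 80 per arm are randomised and 80 x 0.925 = 74 per arm are evaluable at 1 year. The 74 also reproduces: a non-inferiority score test with restricted-likelihood null variance, for 88% versus 97%, margin 2 points, one-sided 0.05 and power 80%, gives 73.6. Nothing below changes that calculation.

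**Set-up.** 80 per arm, no true late difference, unit SD, 4,000 simulated trials per scenario. The probability of loss is logistic in the 4-week score, with a log-odds slope of 0.7 per SD. Correlation between visits is 0.3, 0.5 or 0.7. The slope, the correlations and any loss above 7.5% are assumptions; the protocol gives none of them.

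**Two estimators of the late difference.**

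- Per-visit: mean of observed late scores in one arm minus the other, tested by t-test.
- Using history: in each arm, regress the late score on the baseline and 4-week scores among those observed, then average the predictions over all patients randomised to that arm. This mimics what a longitudinal likelihood model does.

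| Loss mechanism | Per-visit bias (SD) | Per-visit type I error |
|---|---|---|
| 7.5%, unrelated to outcome | at most 0.005 | 0.050-0.057 |
| 20%, same mechanism in both arms | at most 0.004 | 0.052-0.053 |
| 20% v 10%, or 30% v 15%, same slope | 0.02-0.06 | 0.04-0.06 |
| About 7.5%, opposite slopes | 0.03-0.08 | 0.05-0.08 |
| About 20%, opposite slopes | 0.09-0.20 | 0.07-0.20 |
| About 30%, opposite slopes | 0.12-0.28 | 0.10-0.32 |

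The estimator using history had bias of at most 0.007 SD in every row. With 4,000 runs and a standard error near 0.18, simulation error in a mean bias is 0.18 / sqrt(4000) = 0.003.

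**Consistency checks.** The bias should equal the correlation times the gap in 4-week scores between the two arms' attenders, so bias divided by correlation should be constant. At 20% opposite slopes: 0.085/0.3 = 0.28, 0.148/0.5 = 0.30, 0.199/0.7 = 0.28. At 30%: 0.123/0.3 = 0.41, 0.196/0.5 = 0.39, 0.282/0.7 = 0.40. Both agree. The standard error should be sqrt(2/n): with 64 per arm sqrt(2/64) = 0.177, against 0.174-0.182 simulated.

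**A milder mechanism.** In a separate simulation (2,000 trials per setting, four post-treatment visits, correlation 0.5-0.7, assumed dropout of 15-35%), loss before 5 years depended on the 2-year score in one arm only. Bias was 0.08-0.22 SD. Type I error follows from bias/SE: 0.079/0.170 gives 7.5%, 0.144/0.180 gives 12.6%, 0.187/0.194 gives 16.1%.

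**Precision.** With random dropout in that simulation, the per-visit standard error was 1.03 to 1.12 times that of the likelihood estimate. The gain is smaller when loss is small: at 7.5% random loss in the 4,000-run set it was 0.167/0.166 = 1.01 to 0.166/0.162 = 1.02.

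**Scale.** The difference detectable with 80% power, two-sided 0.05, is (1.96 + 0.84) x sqrt(2/n): 0.46 SD with 74 per arm, 0.50 SD with 64 (20% loss) and 0.53 SD with 56 (30% loss). The largest biases are therefore 0.199/0.495 = 40% and 0.282/0.529 = 53% of what the trial could detect at those losses.

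**The case against.** The strongest reply is that the article never says only attenders are analysed. It is silent on missing scores, a t-test or Mann-Whitney U test can be run on imputed data, and imputation rules may sit in a full protocol or analysis plan that is not shown. That stands, and their absence here is not the complaint. What remains is that the article fixes the test, and the test as named neither includes patients without a score nor uses the earlier ones.

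A reader might also infer that the late comparisons are biased as a matter of fact. The documents do not support that. Bias of any size needs loss that relates to the scores differently by arm. The protocol does not say this will happen; the Background's remark that pain and nerve injury after heat treatment can become chronic makes it conceivable, no more. The only documented loss is 7.5%, and at that level even opposite slopes give no more than about 0.08 SD.

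Three further points stand:

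- Loss in the simulations depended on observed scores, which is exactly the condition the alternative needs, so its near-zero bias is by construction. If loss depends on the unseen late state, it can be biased too.
- Mann-Whitney is the likelier test for VCSS. The pilot values in the Background were 3 (IQR 2 to 5) before treatment and 1 (IQR 1 to 2) at 1 year. A normal-theory model fits such a low integer score poorly.
- Clinical success is defined as improvement on VCSS and could be analysed as a proportion by chi-square. That test drops the same patients if run on observed values. AVVQ and SF-36 are not listed under Secondary endpoints.

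**Conclusion.** The point holds in conditional form. Separate two-group tests on observed scores do not deliver what the intention-to-treat label suggests, and they discard scores already collected. The 2- and 5-year comparisons of VCSS, AVVQ and SF-36 may be biased by about 0.1 to 0.3 SD at an assumed 20 to 30% loss if loss depends on earlier scores in opposite directions by arm. Bias is near zero if loss is unrelated to outcome or acts alike in both arms, and small (0.02-0.06 SD) if only the amount of loss differs. Some precision is lost in any case: a 3 to 12% larger standard error at an assumed 15-35% random dropout, about 1 to 2% at 7.5%.

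These sizes rest on assumed loss rates, slopes and correlations, and on no true difference between arms. The 1-year occlusion endpoint and the two-week pain analysis are unaffected. The change is worth making for the long-term clinical claims; it does not threaten the trial's main conclusion.

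**What to change.** For AVVQ and SF-36, replace the visit-by-visit tests with one longitudinal likelihood model over baseline, 4 weeks, 1, 2 and 5 years. Put baseline in the outcome vector, so that every randomised patient with any score contributes. Use arm-by-visit terms and an unstructured covariance, and read the arm difference at 1, 2 and 5 years from the model.

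For VCSS, use the same structure with robust or bootstrap inference, or an ordinal model. Alternatively, keep the Mann-Whitney U test after multiple imputation that uses the earlier scores.

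State what intention-to-treat means for a patient without a late score. If such rules already exist in a fuller document, refer to them.

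The cost is analysis wording only; all the scores are already scheduled. The price is an assumption that scores are missing at random given those observed, and for VCSS some added modelling assumptions that a plain rank test avoids.
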